**STUDY SYNOPSIS**

| Protocol No. | TG0508YIC |
| --- | --- |
| Title | Efficacy, safety of therapeutic hepatitis B vaccine (YIC) among chronic hepatitis B patients: a multi-center, randomized, double-blinded, controlled phase IIB clinical trial |
| Version | 2nd version, Oct 24, 2005 |
| SPONSOR | Beijing Vaccine Institute, and Shanghai Medical College, Fudan University |
| Phase | Phase IIB |
| Study population | Chronic hepatitis B patients |
| Objective | - To study the tolerance and efficacy of YIC among chronic hepatitis B patients through the comparison between 30 μg, 60 μg YIC and placebo groups. - To study the optimal regimen |
| Study design | Double-blinded, randomized, placebo-controlled trial with basic treatment. Subjects will be assigned to 30 μg, 60 μg YIC and placebo group equally. |
| Sample size | 240 patients |
| Number of study center | 12 |
| Duration | 44 weeks (0- 20 weeks treatment plus 24 weeks follow-up) |
| Selection Criteria | Inclusion criteria:   1. Patients with chronic hepatitis B aged 18 to 65 years; 2. Patients with > 6 months HBsAg positive prior to study; 3. HBeAg positive, HBeAb negative, and HBV DNA  1105 copies/ml; 4. Patients with ALT abnormal (2-fold higher but 10-fold less than cutoff at baseline.)   Exclusion criteria:   1. Co-infection with hepatitis A, C, D and E virus, or HIV; 2. Taking antiviral, hepatotoxic or immunosuppressive drugs or products within the preceding 6 months; 3. Other causes of liver disease; 4. Serious medical or psychiatric illness; 5. Hepatic cirrhosis or AFP>100 ng/ml; 6. Abnormal serum creatinine, thrombocyte count, 7. Hematoglobin or serum total bilirubin abnormal; 8. And pregnancy |
| Study agent | Vaccine:：therapeutic hepatitis B vaccine, 60 μg per ampoule.  Placebo：0.1% alum, 1 mL per ampoule |
| Study arm | Three arms, 80 cases for each.  Vaccine groups: 30 μg YIC and 60 μg YIC  Control group: placebo |
| Endpoints | The virologic response was assessed four weeks after the end of treatment (week 24) and at the end of follow-up (week 44). HBeAg seroconversion was defined by the loss of HBeAg and the presence of anti-HBe antibody. Suppression of HBV DNA was defined as > 2 log10 decrease of viral load.   - The primary endpoint was defined as loss of HBeAg, or presence of anti-HBe antibody or suppression of HBV DNA. - The secondary endpoint was designated as both HBeAg seroconversion and suppression of HBV DNA. |
| Safety endpoints | Adverse events, laboratory testing, systemic and local reactions. |
| Study procedure | - After the protocol being approved by the ethic committee, and inform consenting, patients will be screened and assigned to 30 μg, 60 μg YIC and placebo groups randomly; - Study agents will be given at baseline (0 week), 4th, 8th, 12th, 16th and 20th week; - Treatment will be ended at 20th week, and followed both at 24th week and by 44th -week for efficacy follow-up; - Subjects will be interviewed at baseline, 4th, 8th, 12th, 16th, 20th, 24th, 36th, and 44th week. Each interview will include blood cell count and biochemical liver function testing. Virologic and HBeAg/anti-HBe from samples of all patients will be assayed at the same time for serum at baseline, 12th, 24th, 36th, and 44th week at the reference lab after 44-week follow-up. - Adverse events, and concomitant medication will be recorded at each interview. |

# STUDY TITLE

Efficacy, safety of therapeutic hepatitis B vaccine (YIC) among chronic hepatitis B patients: a multi-center, randomized, double-blinded, controlled phase IIB clinical trial

# Rationale

- 1. General Introduction

Viral hepatitis B is highly endemic in China, with estimated 130 million chronic hepatitis B surface antigen carriers. Of these, 30 million infected individuals are chronic active hepatitis patients who need antiviral therapy, which mostly relies on interferon  and lamivudine. The short-term efficacy response to interferon  is 40-60%, which reduces to 20-40% one year after the treatment, and its use is associated with dose-related side effects. For lamivudine, after one year consecutive treatment, the loss of HBeAg reaches 20-25%, and HBeAg seroconversion rate is 15-20%. However, the use of lamivudine for more than 6 months is associated with the emergence of resistant YMDD variants. Furthermore, rebounds of HBV DNA are frequently observed after longer period of treatment. Hence, effective immuno-modulating drugs or products to enhance host immune responses aiming to break immune tolerance to hepatitis B virus (HBV) is encouraged.

The therapeutic hepatitis B vaccine (Yeast derived Immunogenic Complex, YIC), consisting of immune complexes of HBsAg and high titer of human anti-HBs immunoglobulin (HBIG) at an appropriate ratio, is developed by the Key Laboratory Medical Molecular Virology, Shanghai Medical College, Fudan University with the financial support of 863 National Program. It possesses Chinese patent**.** Pre-clinical animal experiments revealed that, YIC was able to clear circulating HBeAg, induce anti-HBs, INF- and CTL in transgenic mice. The YIC vaccine was formulated under GMP by Beijing Vaccine Institute and has passed the qualification by the National Institute for the Control of Pharmaceutical and Biological Products. The GCP-compliant phase I and phase IIa clinical trials was conducted by Beijing Ditan Hospital in 2003 and 2004 respectively. The safety and tolerance of 30 g、60 g, and 90 g YIC with 3-dose regimen and 6-dose regimen of 90 g YIC have been proved in phase I trial. Subsequently, 36 chronic hepatitis B patients were assigned to placebo group, 60 g and 90 g YIC groups randomly in Phase IIa trial. All participants were immunized with six intramuscular injections at 4- week intervals, and followed to 44th week. A basic treatment (Silymarin, 50 mg per tablet, 3 tablets per time, tid; and Hu Gan Pian tablet, an extraction of Chinese herb containing Wu Wei Zi) which has proved to be effective for improving liver function, 0.36 g per tablet, 4 tablets per time, tid) was given to each participant of all groups throughout the 44-week period. After the termination of immunization, serum samples were collected from each patient at baseline, 12th, 24th, 36th and 44th week after initial injection for assay of HBeAg, anti-HBe, HBV DNA, and alanine aminotransferase (ALT). Because immune responses to immunotherapy should be monitored some time later after the last injection, four weeks after the end of treatment (24th week)and follow-up for 24 weeks ( 44 week) were set for the time points in this study. Suppression of HBV DNA (less than 1.0*105 copies/mL) was found in 4 patients, one was in the placebo group, the other three were in 60 g YIC group, none was found in 90 g YIC group. HBeAg seroconversion was found in two patients in 60 g YIC group. The most common adverse event in phase IIa trial was local reaction at injection site, .Almost all adverse events were mild. In some participants temporary elevated ALT was observed, which recovered to normal levels at follow up. Serious adverse event was not observed.

- 1. Rationale of dosage

In terms of the conclusion of phase IIA, efficacy of 60 g YIC group was better than 90 g YIC and placebo groups. However, phase IIA trial was not able to exclude the possibility that 30 g YIC might be the optimal dosage. Therefore, both 30 g and 60 g YIC will be included in the phase IIB study to work out the optimal dosage through the comparison with placebo control.

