# Objectives

- To study the tolerance and efficacy of YIC among chronic hepatitis B patients through the comparison between 30 g, 60 g YIC and placebo groups.
- To optimize dosage and regimen

1. Study Disgn

This is a double-blinded, randomized, placebo-controlled trial with basic treatment.

- 1. Study agent

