#### Vaccination

Study agents will be administrated to each patient according to the allocation number on the label of study agent.

Precaution

1. Products should be shaken thoroughly prior to administration;
2. Products should be inspected visually for particulate matter or discoloration prior to administration;
3. Epinephrine should be available for potential immediate allergic reactions;
4. Injection should be carried out by experienced and per-designated personnel;
5. All used study agent-related things including empty ampoules, packages and labels should be kept;
6. To ensure the accuracy of dosage, one mL syringe should be used for injection.

Study agent code will be assigned strictly to patient in terms of the recruitment sequence. All instruction on the label of study agent will be followed.

Administration

With thorough agitation, 1 mL (for either 30 g YIC group or 60 g YIC group) vaccine will be drawn from ampoule using 1 mL syringe, and will be injected to patient in the deltoid region. The injection will be given at day 1, week 4, 8, 12, 16 and 20.

With thorough agitation, 1 mL placebo will be drawn from ampoule using 1 mL syringe, and will be injected to patient in the deltoid region. The injection will be given at day 1, week 4, 8, 12, 16 and 20.

A total of 240 chronic hepatitis B patients will be recruited, and assigned to 30 g (group 2), 60 g YIC (group 3), and placebo group (group 1) in a ratio of 1:1:1.

The immediate reaction within 30 minutes after injection will be observed. Concurrently, basic medication (Silymarin and Hu Gan Tablet) will be distributed to each participated patient. To record the solicited and non-solicited reaction in the following 4 weeks after injection, diary card will be distributed. Corresponding instruction for filling in out will be given by investigator.

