# Statistical Methods

All data will be double entered into custom-made data entry programs. The data management programs include range and consistency checks. An SAS program (SAS Institute Inc., Cary, NC, USA ) will be applied for statistical analysis.

- 1. Safety

The safety analysis will be performed based on the safety set (SS). It will include patients who received at least one injection, and completed at least one interview of safety evaluation after injection.

Three-wise comparison employed the chi square test, or Fisher’s exact test when data were sparse, for dichotomous outcomes will be performed to test the difference of occurrence of adverse events among placebo, 30 μg YIC and 60 μg YIC groups. A p-value < 0.05 (two-tailed) will be considered statistically significant.

- 1. Efficacy

The efficacy analysis will be conducted based on both full analysis and per-protocol sets. For full analysis set (FAS), it will include patients who were randomized, received at least one injection, and completed at least one interview of efficacy evaluation after injection. The intent-to-treat principle will be applied for the dataset. For per protocol set (PPS), it will include patients who met following three conditions：

1. Baseline information are available；
2. Complete full course of treatment and follow-up without protocol violation；
3. With good compliance (between 80% and 120%）.

For those important indicators, the missing data will be estimated using the most previous observation (LOCF, last observation carry forwards).

The primary efficacy hypotheses will be tested for response rate of primary endpoint in 30 μg YIC or/and 60 μg YIC groups > that in placebo group (2-tailed). The Chi square test, or Fisher’s exact test when data were sparse, will be employed. A p-value, point estimate, as well as confidence interval will be calculated.

The secondary efficacy outcomes will be summarized in a similar fashion.

Repeated measures analysis will be performed using a generalized estimating equations (GEEs) method to adjust the dependence among repeated observations made on the same patient while testing the group and time effects. A p-value < 0.05 (two-tailed) will be considered statistically significant.

- 1. Sample size

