The sample size was calculated to ensure an adequate evaluation of the primary endpoint. Based on the literatures and the results of phase IIa trial, a sample size of 78 patients per arm could detect a difference of primary response rate between 60 µg group, 30 µg group and placebo group (response rate in 60 µg YIC group vs placebo group, 35% vs 3%; and response rate in 30 µg YIC group vs placebo group, 20% vs 3%) with a statistical power of 80% at the 0.05 level of significance, allowing for a dropout rate of 20%.

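### The stated aim of optimising dosage and regimen outruns the design: no arm varies the regimen, and the stated route through placebo cannot rank the two doses

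*Protocol*

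**What the plan says.** - **Objectives.** Section 3 of the protocol gives the second objective as "To optimize dosage and regimen". The synopsis words it as "To study the optimal regimen". The first objective is broader: "To study the tolerance and efficacy of YIC among chronic hepatitis B patients through the comparison between" the 30 µg, 60 µg and placebo groups.
- **Route to the dose.** Section 2.2 says 30 µg and 60 µg are both included "to work out the optimal dosage through the comparison with placebo control".
- **Schedule.** Section 4.3.3 uses the same sentence for vaccine and for placebo: "The injection will be given at day 1, week 4, 8, 12, 16 and 20".
- **Efficacy analysis.** The primary hypotheses in section 6.2 set the 30 µg and/or 60 µg response rate against placebo, by chi-square, or by Fisher's exact test for sparse data. A p-value, point estimate and confidence interval are to be given. Secondary outcomes are handled similarly, and a GEE analysis tests group and time effects without naming contrasts.
- **Safety analysis.** Section 6.1 plans a three-way test, "to test the difference of occurrence of adverse events among placebo" and the two doses.
- **Sample size.** Section 6.3 gives 78 per arm for 35% versus 3% (60 µg versus placebo) and 20% versus 3% (30 µg versus placebo), with 80% power, a 0.05 level and 20% dropout. The synopsis plans 80 per arm.

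**The concern.** An objective needs a contrast in the design that can address it. For regimen there is none. For dosage, the contrast exists in the randomisation, but the protocol points to a different one. Two separate tests against placebo answer whether each dose works. If both succeed, they give no basis for choosing between the doses. If only one succeeds, that does not show that the doses differ.

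At stake is the dose and schedule carried into the next trial. A claim about regimen would have no randomised support. A claim about dose could be made with its uncertainty never stated, because no 60 versus 30 µg efficacy estimate is named and the trial is not sized for one.

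**Working it through.** **Regimen.** Section 4.3.3 fixes six injections at the same times in all three arms. Section 2.1 uses the word regimen for the number of injections (three or six) in the phase I trial, so it is not simply a synonym for dose level in this protocol. If it means number or timing of injections, nothing is randomised and no analysis can recover it.

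**Dosage: inputs.** Response rates are 3% (placebo), 20% (30 µg) and 35% (60 µg), two-sided α = 0.05, from sections 6.2 and 6.3. There are 80 per arm (synopsis). Assumption: 20% dropout leaves 80 × 0.8 = 64 evaluable. Carrying the last observation forward in the full analysis set could bring the analysed number nearer 80, so both are shown.

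**Step 1. The plan's own figure.** For 20% versus 3%, mean rate 0.115:

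n = [1.96·√(2·0.115·0.885) + 0.8416·√(0.20·0.80 + 0.03·0.97)]² / 0.17² = 54.1

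The continuity correction gives (54.1/4)·[1 + √(1 + 4/(54.1·0.17))]² = 65.3, and 65.3 × 1.2 = 78.4. The stated 78 is therefore reproduced from the 30 µg versus placebo contrast. The protocol does not state its formula; this is the variant that fits.

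**Step 2. What the placebo tests would show.** I take a simulation of 200,000 trials, with each dose tested against the shared placebo arm by chi-square.

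| Truth | Result | 64 per arm | 80 per arm |
|---|---|---|---|
| 35%, 20%, 3% | both doses beat placebo | 90.4% | 95.4% |
| 35%, 20%, 3% | only 60 µg does | 9.6% | 4.6% |
| 20%, 20%, 3% | only one dose does | 13.5% | 7.4% |

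In the last row the doses are identical, and the split is even: 6.7% plus 6.8% with 64 per arm, 3.7% plus 3.8% with 80 (sums taken before rounding).

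**Step 3. A direct 35% versus 20% comparison.** Mean rate 0.275. Approximate power is Φ{[0.15·√n − 1.96·√(2·0.275·0.725)] / √(0.35·0.65 + 0.20·0.80)}:

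- n = 64: Φ[(1.200 − 1.238)/0.622] = 47.6%; exact enumeration of the chi-square test gives 48.4%.
- n = 80: Φ[(1.342 − 1.238)/0.622] = 56.6%; exact 57.6%.

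For 80% power: n = [1.238 + 0.8416·0.622]²/0.15² = 137.9, so 138 evaluable per arm.

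**Step 4. Precision.** The 95% half-width is 1.96·√[(0.35·0.65 + 0.20·0.80)/n], which is 0.153 for n = 64 and 0.136 for n = 80.

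**Step 5. Ranking by observed rate.** In the same simulation at the planned rates, 60 µg had the higher observed rate in 96.6% (n = 64) and 98.0% (n = 80) of trials.

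**The case against.** A reader might infer that the protocol compares the doses only with placebo. It does not: the first objective spans all three groups, the safety test is three-way, and the GEE tests group effects. The accurate statement is narrower: no 60 versus 30 µg efficacy contrast is named.

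A reader might also infer that the dosage question cannot be answered. That is too strong. Two doses are randomised concurrently, and a phase IIB choice can rest on estimates. Section 6.2 asks for point estimates and intervals. When two rate differences against the same placebo arm are subtracted, the placebo rate cancels and leaves the dose difference. Step 5 shows that the observed ordering would usually be right if the planned rates are true. What is missing is the precision of that difference.

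Nor does the protocol say that the dose will be chosen by which p-value crosses 0.05. At the planned rates the likelier outcome is that both cross.

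Finally, pairwise contrasts are often left to a statistical analysis plan, which is not at hand. Silence in section 6.2 alone would therefore be weak grounds. But section 2.2 is not silent: it states a route that does not rank the doses. And no analysis plan can supply a regimen contrast that the design lacks.

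**Conclusion.** For regimen the point holds in full, unless the word is meant as dose level only, in which case the protocol should say so. For dosage it holds in limited form: the stated route does not rank the doses, and the trial is sized for the placebo contrasts alone. A direct comparison falls well short of the conventional 80% power, because 138 evaluable per arm would be needed against 64 to 80 available.

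These figures rest on the plan's assumed rates, the chi-square test that section 6.2 makes the default, and 64 to 80 analysed per arm. The share of trials with a misleading split result rests on a further assumption, that both doses truly give 20%. The placebo-controlled primary analysis is unaffected.

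**What to change.** 1. In the synopsis and section 3, remove regimen from the second objective, or define it as dose level only, and state that dose selection is exploratory.
2. In section 2.2, replace the reference to placebo as the route to the dose with a direct comparison of the two doses.
3. In section 6.2, add the 60 minus 30 µg difference in primary response with its 95% confidence interval, at the protocol's two assessment times (weeks 24 and 44). State the expected half-width of about 14 to 15 points.
4. State that significance against placebo in one arm only will not be used to rank the doses.

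This needs no extra patients, visits or assays. The cost is a narrower stated objective and one additional estimate from data already collected.

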# Objectives

- To study the tolerance and efficacy of YIC among chronic hepatitis B patients through the comparison between 30 g, 60 g YIC and placebo groups.
- To optimize dosage and regimen

1. Study Disgn

This is a double-blinded, randomized, placebo-controlled trial with basic treatment.

- 1. Study agent

### Vaccine

Therapeutic hepatitis B vaccine (commercial name: YIC, Lot: 20050501), 30 g or 60 g per mL per ampoule, manufactured by Beijing Vaccine Institute, and stored at 2 to 8oC.

### Placebo

Placebo consists of 0.1% alum adjuvant, 1 mL per ampoule. It is manufactured by Beijing Vaccine Institute with the identical appearance of vaccine.

- 1. Study population

Chronic hepatitis B patients will be evaluated and recruited at each treatment center in the trial. Following inclusion and exclusion criteria will be employed for eligibility evaluation.

### Inclusion criteria

- 1. Patients provide written inform consent;
  2. Patients aged 18 to 65years regardless of gender;
  3. Patients with HBsAg positive in the preceding 6 months;
  4. Patients with HBeAg positive, HBeAb negative, and virus load (HBV DNA)  1105 copies/ml;
  5. Patients with abnormal ALT (between 2- and 10-fold of cutoff value). If abnormal ALT had appeared in the preceding 6 months, the interval period should be longer than one month;
  6. For reproductive age women, the uric or blood pregnancy test should be negative. Both male and female patients should not have birth plan until 3 months after the completion of study.

### Exclusion criteria

1. Pregnancy women or lactation women;
2. Patients who have received antiviral therapy or immunosuppressive drugs, such as adrenal cortical hormone, thymic peptide 1 in the preceding 6 months or long-term;
3. Patients co-infected with HAV, HCV, HDV, HEV and HIV;
4. Patients with history of or current allergic diseases, hypersensitivity to any biological product injection, and autoimmune diseases;
5. Patients who have received hepatotoxic drugs in the preceding 6 months;
6. Patients with confirmed or suspected liver cirrhosis, or compensated cirrhosis;
7. Patients with confirmed or suspected primary hepatic carcinoma or AFP>100ng/ml;
8. Patients with other liver diseases, including chronic alcoholic hepatitis, drug-induced hepatitis, autoimmune hepatitis（antinuclear antibody > l:100）、Kinnier-Wilson syndrome, and hemachromatosis;
9. Life-threatening or serious cardiac, respiratory, gastrointestinal, renal, endocrine, hematological or immunological disorders which, in the opinion of the investigator, will be **excluided** in the study;
10. Serum creatinine > 1.5-fold of upper limit of cutoff value;
11. Blood platelets count < 75×109/L；
12. Leucocyte count < 3×109/L；
13. Haematoglobin <11.5g/dL（female） or <12.5g/dL（male）;
14. Serum total bilirubin  2-fold of upper limit of normal value;
15. Patients with history of drug addiction, including alcohol abuse (40g/day) in the preceding 6 months;
16. Patients had participated in other clinical trials in the preceding 3 months.
    1. Study procedure

The core procedures see appendix 2. The entire study duration will be 46 weeks, including 2-week run-in, 20-week treatment and 24-week follow-up.

### Informed consent

Informed consent must be obtained from each potential patient to be enrolled in the study. The information in the consent form should be communicated to the patient in language that they can understand. The consent form and any subsequent revisions must be reviewed by the Institutional Review Board (IRB) overseeing the study.

### Screening (two weeks prior to treatment)

After signing the informed consent,, every potential participant will be assigned a screening number. Screening will be performed in a two-week period prior to the treatment in terms of the inclusion/exclusion criteria. Following investigation of medical history, including family history on hepatitis B infections, and physical examination (temperature, heart rate, and blood pressure), a series of tests will be performed:

1. X-ray[[2]](#footnote-2), type B ultrasonic (liver, spleen and gallbladder)[[3]](#footnote-3), electrocardiogram;
2. Urine or blood HCG pregnancy test[[4]](#footnote-4);
3. Serum HBeAg、HBsAg、HBsAb 、HBeAb、HBcAb;
4. Liver function, including ALT、AST、TBil、DBil、TP、ALB、AKP;
5. Biochemistry tests, including blood cell count, microscopy[[5]](#footnote-5), uric testsd, renal function and electrolytes;
6. PTA;
7. Blood glocuse;
8. Anti-HAV IgM, anti-HDV，and anti-HEV;
9. Anti-HCV, and anti-HIV;
10. Antinuclear antibody;
